### 4.6. Statistical Analysis

Statistical analysis will be conducted through IBM SPSS 22.0. The primary purpose of this protocol is to discover the connection between the relief of pain or discomfort post-operation and the medical staff’s psychological intervention. Primary outcomes will be estimated to determine the statistical significance (at a significance level of 0.05). Other outcomes and different endpoints aiming at illustrating the patient’s psychological conditions and the rehabilitation situations would also be analyzed. Descriptive analysis will be conducted to explore the effects of subgroups based on specific surgical techniques. Analysis of covariation (ANCOVA) will be used to assess changes in various time points, offering evidence at a 95% confidence interval to evaluate the effects on the final clinical result. SDs and outcomes in each time point at the mean change will comprise descriptive statistics and linear regression random-effects models will be used to describe the differences in mean changes between the groups.

As for the underlying missing data or incomplete adherence in this protocol, regardless of normal study attrition, steps to minimize the loss of follow-ups and maximize adherence to the rehabilitation program will be taken. A sensitivity analysis will be conducted to analyze the missing data and their potential effect on the final result, as well as an evaluation of the baseline comparability between the traditional rehabilitation group and the psychological intervention group. Any changes in protocol design will be recorded with reasonable justifications.

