## Abstract

Purpose: The purpose of this protocol was to discover the connection between patients with non-surgical pain or other discomfort and their psychosocial status. Cognitive behavior therapy will be used, which we verified will determine the effect and feasibility of postoperative rehabilitation processes. Materials and Methods: This study will include 200 patients ranging from 18 to 60 years old who have underwent or will undergo FAI arthroscopy in the West China Hospital Sports Medicine Center from 2023 to 2026. A standardized prospective single-center parallel-group randomized controlled trial will be used for these participants. The participants will be divided into intervention (telephone versus face-to-face versus music versus floatation) and control groups. The follow-up periods will be measured pre-operatively, as well as postoperatively at 1, 3, and 6 months. The primary outcomes will include the modified Harris Hip Score (mHHS) and the Visual Analogic Score (VAS), and the secondary outcomes will include the range of motion (ROM), the Huaxi Emotional-distress Index (HEI), and the depression, anxiety, and stress scale (DASS-21 scale). Furthermore, the Patient Health Questionnaire-9 (PHQ-9) and a Short-Form 12 (SF-12) questionnaire will also be evaluated. Discussion: This study will evaluate the clinical and cost-effectiveness of different types of psychosocial-therapy-based rehabilitation methods designed to improve the quality of life of FAI patients with persistent symptoms.

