Additionally, patients after total hip or knee arthroplasties with infection suffered from psychological burdens, implying a correlation [9]. Bay et al. performed a systematic psychological evaluation of total hip arthroplasty (THA) patients and found that psychological interventions were not routinely applied for THA; therefore, determining the applicable conditions for and optimal usage of THA is still required [10]. Additionally, there were no comparisons between different psychosocial interventions in FAI patients in the literature.

Therefore, this trial’s primary objective is to compare the effectiveness of different psychosocial therapies for improving the quality of life of FAI participants with persistent postoperative symptoms. The secondary objective is to determine the relationship between clinical effectiveness, patients’ feedback, and relative cost-effectiveness.

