### 2.3. Randomization and Allocation Concealment

The randomization schedule will be completed by the study biostatistician’s computer-generated random numbers table. The allocation ratio will be generally equal for patients allocated in the five groups mentioned above. Participants and physiotherapists will both receive random numbers sealed in envelopes. The matching envelopes will be allocated and stored by a researcher not participating in any recruitment, treatment, or assessment process.

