### 4.5. Sample Size

The primary endpoint will be altered from baseline to 6 months post-surgery in the mHHS scale. A pilot trial was conducted, and the baseline suggested the targeted patients’ population, with a mean mHHS of 85.1 and an SD of 8.7. The minimal clinically important difference (MCID) for the mHHS scale in this population is 8 points [29,42]. Therefore, the sample size of this study will be calculated based on the mHHS SD of 8.7 and the MCID of 8.

G*power software (version 3.1.9.7 for Windows XP, Vista, Germany) was used to calculate the sample size, with an effect size of 0.8 and power of 90%, and a sample size of 34 in each group is required for the minimum inclusion. Considering the allowance of 15% for a loss of follow-up for 12 months postoperatively, 40 participants will be recruited in each group.

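### The sample size powers one two-arm comparison, but the trial has five arms and aims to compare therapies, and no contrast is named for the single 0.05 level

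*Protocol article*

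**What the plan says.** All statements are from the Protocol article.

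- **Arms (Abstract; 2.3).** "The participants will be divided into intervention (telephone versus face-to-face versus music versus floatation) and control groups". On allocation: "The allocation ratio will be generally equal for patients allocated in the five groups mentioned above".
- **Objective (1. Introduction).** "this trial’s primary objective is to compare the effectiveness of different psychosocial therapies". With four active arms this is a therapy-versus-therapy question.
- **Sample size (4.5).** The inputs are given as "the sample size of this study will be calculated based on the mHHS SD of 8.7 and the MCID of 8". The calculation is then reported "with an effect size of 0.8 and power of 90%, and a sample size of 34 in each group is required for the minimum inclusion". Finally: "Considering the allowance of 15% for a loss of follow-up for 12 months postoperatively, 40 participants will be recruited in each group". The section names mHHS change from baseline to 6 months as the primary endpoint. It states neither alpha nor sidedness.
- **Analysis (4.6).** "Primary outcomes will be estimated to determine the statistical significance (at a significance level of 0.05". ANCOVA and random-effects linear regression are listed for changes over time and differences between groups. No reference arm, primary contrast or family of contrasts is named.

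**The concern.** Three stated parts of the plan do not fit together. The objective calls for several comparisons among therapies, the sample size delivers the stated power for one comparison of two groups, and the 0.05 level is attached to no particular contrast.

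Two things are at stake. A claim that one therapy works, or is better than another, could carry an error rate several times 5% if every pair is judged at 0.05. And if the family is protected instead, the advertised 90% no longer describes the comparisons the trial will report, at the effect size the protocol used. The Discussion says the trial can guide clinical decisions about rehabilitation programmes, so the claim about a particular therapy is the one that matters.

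**Working it through.** **Inputs.** Effect size d = 0.8, power 90%, 34 per group, SD 8.7, MCID 8 and 15% loss (4.5); five roughly equal arms (2.3); level 0.05 (4.6). Assumption: two-sided 0.05 in the sample-size calculation.

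**1. Reproduce the plan's figure.** For a two-sample t-test the noncentrality is d × √(n/2) = 0.8 × √17 = 3.30, with 2 × 34 − 2 = 66 df. Power is 0.9015 at n = 34 and 0.893 at n = 33, so 34 is the smallest n reaching 90%. Inflation: 34/(1 − 0.15) = 40 per arm, and 5 × 40 = 200. The plan's figures reproduce exactly.

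Other variants tried do not give 34:
- one-sided 0.05: 28
- d = 8/8.7 = 0.92, two-sided: 26
- five-group ANOVA: 51 per group at f = 0.25, 21 per group at f = 0.40

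This supports the inference of one pairwise, two-sided 0.05 test.

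**2. Number of contrasts.** Four therapies against control: 4. Pairs among four therapies: 4 × 3/2 = 6. All pairs among five arms: 5 × 4/2 = 10.

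**3. False positives if each contrast is tested at 0.05.** Simulation of five arms with 34 each, no true effects, one outcome, pooled variance with 5 × 34 − 5 = 165 df:

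| Family | At least one p < 0.05 |
|---|---|
| 4 versus control | about 15% |
| 6 therapy pairs | about 20% |
| 10 pairs | about 28% |

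These are below the independence values 1 − 0.95^k (18.5%, 26.5%, 40.1%) because contrasts that share an arm are correlated.

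**4. Power per comparison at 34 per arm with family-wise control at two-sided 0.05.** Power is the probability that a noncentral t with noncentrality d × √17 exceeds the critical value. The noncentrality is 3.30 at d = 0.8 and 3.79 at d = 0.92.

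| Method | Critical value (t scale) | d = 0.8 | d = 0.92 |
|---|---|---|---|
| Unadjusted | 1.97 | 91% | 96% |
| Dunnett, 4 versus control | 2.46 | 80% | 91% |
| Tukey, 4 active arms | 2.60 | 76% | 88% |
| Tukey, 5 arms | 2.76 | 70% | 85% |

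(The unadjusted 91% exceeds the 90.2% of step 1 because the pooled variance has 165 df rather than 66.)

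**5. Size needed for 90% per comparison at d = 0.8.** Before dropout, about 44 per arm with Dunnett and 51 with Tukey on five arms, against the planned 34.

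**The case against.** **Multiplicity is commonly left to the SAP, which is not shown.** This stands in part. An SAP may well name an adjustment, and the missing adjustment is not the point here. But an SAP cannot restore the protocol's power statement: at d = 0.8 and 34 per arm, each adjustment examined falls clearly below 90%.

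**The 0.05 may be an overall level.** This stands. A reader might infer that false positives are uncontrolled, but 4.6 does not say that each pair is tested at 0.05. The 15%, 20% and 28% are conditional on that reading. A five-group ANCOVA could also supply an overall F-test first, which would hold the error at 5% when no therapy differs from any other arm. It would not protect the remaining comparisons once one arm truly differs, and it has about 74% power at 34 per arm if only two arms differ, by 0.4 SD either side of the rest.

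**The 90% survives on the protocol's own clinical inputs.** This stands for one family only. At 8/8.7 = 0.92, Dunnett against control gives about 91%. The Tukey families give 88% and 85%, and it is these that match the objective as worded.

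**4.6 seems to plan a pooled analysis.** A reader might infer a pooled outcome contrast from "baseline comparability between the traditional rehabilitation group and the psychological intervention group". The sentence concerns baseline comparability only and sets no outcome test, so it is not counted here. A single prespecified pair, or a pooled contrast, would need no adjustment across arms. Neither is named, and a pooled contrast could not answer the stated objective.

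**Separate therapies sharing a control need not be adjusted.** This is debated in general. It carries less weight where the declared aim is to compare the therapies with one another.

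**Conclusion.** The point holds in this form: the sample size is one two-arm calculation, placed in a five-arm trial whose primary objective needs several contrasts, with a single 0.05 level tied to none of them.

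Under family-wise control at 34 per arm and d = 0.8, power per comparison is about 70% to 80% rather than 90%. At d = 0.92 it is about 85% to 91%. If no control is applied, the chance of some false positive on 6-month mHHS is about 15% to 28%, depending on the family.

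These figures assume two-sided 0.05, equal arms, equal variances, the protocol's 15% loss, and one primary endpoint (6-month mHHS change). The Abstract also lists VAS as a primary outcome. Error rates across both outcomes would be higher, but they depend on a correlation that the document does not give, so no such figure is relied on here.

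**What to change.** Before data are seen, the sponsor should:

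1. Name one primary family of contrasts on 6-month mHHS that matches the objective. Either keep the objective and use the therapy-versus-therapy pairs (or all pairs) with Tukey, or use the four therapy-versus-control contrasts with Dunnett and reword the objective in the Introduction to match. The second option changes the trial's stated question, so it is a decision and not an edit.
2. State in 4.5 and 4.6 that two-sided 0.05 is the overall level for that family.
3. Label all other contrasts secondary.
4. Restate power per comparison for the chosen family and effect size at the planned 200 patients (34 evaluable per arm), using the table above. Say whether 0.8 or 8/8.7 = 0.92 is the effect size, since the two are not the same.

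The planned 200 patients need not change, and the work is confined to wording. The cost is slightly wider intervals and a less favourable power figure. If 90% per comparison is to be kept at d = 0.8, the sample would have to grow as in step 5 of the working.

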## 5. Discussion

This study provides a protocol for a randomized controlled trial to identify practical operability and clinical- and cost-effectiveness, as well as to determine participants’ satisfaction. This trial will assist in identifying the relationship between a patient’s subjective feelings and unwell symptoms, as well as the underlying psychosocial factors, by offline supervised training, therapy adjustment, and long-term follow-ups, enabling further improvements in treatment strategies.

Recent studies have shown that although pain is one of the major factors contributing to clinical outcomes and patients’ satisfaction, there is still a considerable need for high-quality RCT to develop optimal pain management strategies with minimal complications [4]. In addition, researchers have reported that psychological factors may increase pain severity [16,43,44,45]. Renee et al. [43] reported an amplification of somatic symptoms, including headache, abdominal pain, and impairment, due to depressive emotions. Furthermore, Maria et al. [44] and P. Cristancho et al. [45] also reported that increasing pain resulted from emotional dysfunction for elderly patients and patients with hip fractures. The research above supports the hypothesis that psycho-related problems result in increased severity of pain or discomfort; however, there is still a lack of high-quality evidence.

Other related studies have documented psycho-social factors affecting postoperative symptoms in other regions of the human body. Six studies reported an association between psychological factors and postoperative pain after knee surgeries [46,47,48,49,50,51]. Traditionally, psychological problems before surgery are more common than after surgery, and as for the latter period, post-operation follow-ups after 3, 6, and 12 months were primarily used for the identification [52,53]. Particularly, four of the six selected articles reported significant changes in psychological conditions when catastrophizing pain scores [46,47,50,51]. Furthermore, one merely explored the importance of psychosocial evaluation for interventions associated with pain and functional outcomes after surgery [49], while the others indicated no significant changes in the clinical outcomes [48].

The limitations of this study include the impossibility of participants and researchers being blinded in clinical trials; furthermore, the possibility of assessor bias cannot be discounted. Other factors, such as the participant’s practical adherence and completeness towards rehabilitation programs and psychological interventions should also be considered.

The innovations of this trial include: 1. this protocol is the first RCT study in psychosocial treatment for FAI participants with persistent postoperative symptoms; 2. the psychosocial treatment and staged assessment can be personalized, with therapy adjusted accordingly; and 3. this trial can guide the clinical decision making of targeted postoperative rehabilitation programs, developing indispensable interventions for future applications.

## Figures and Tables

**Figure 1 jcm-12-03612-f001:**
[figure not shown]
A flow diagram of the study protocol.

**Table 1 jcm-12-03612-t001:** Summary of outcome assessments and data collection measures.

T0 assessment: baseline	mHHS, ROM, VAS, DASS-21, PHQ-9, HEI, SF-12
T1 assessment: 1 month	mHHS, ROM, VAS, DASS-21, PHQ-9, HEI, SF-12, clinical significance
	**plan adjustment**
	symptom↑ or participant’s feedback of heavy burden: adjust participant’s condition, decrease training volume or time smoothly, and drug usage if necessary
	symptom↓ or participants feedback positive: continue or increase training time smoothly
T2 assessment: 3 months	mHHS, ROM, VAS, 6-min walk test, DASS-21, PHQ-9, HEI, SF-12, clinical significance
T3 assessment: 6 months	mHHS, ROM, VAS, 6-min walk test, DASS-21, PHQ-9, HEI, SF-12, clinical significance, satisfaction, cost-effective analysis

mHHS: modified Harris Hip Score; VAS: Visual Analogic Score; ROM: range of motion; HEI: Huaxi Emotional-distress Index; DASS-21: depression, anxiety, and stress scale; PHQ-9: Patient Health Questionnaire-9; SF-12: Short-Form 12.

## Data Availability

Evaluation scales have been submitted in the Supplementary Materials.
